### 2.6. Description of the Intervention

The intervention consisted of two curriculum components, SGC intervention and SP intervention, with the SGC intervention curriculum consisting of three modules of practical gardening intervention, theoretical gardening and nutritional intervention and culinary intervention, and the SP intervention curriculum consisting of two modules of practical motor skills intervention and theoretical exercise health curriculum, with information about the specific intervention components shown in Table 1.

#### 2.6.1. SGC Intervention

Members of the project team received training from the Texas A&M AgriLife Extension Service and received Proof of completion certification and extension authorization. The SGC intervention was adapted from the Junior Master Gardener Health and Nutrition from the Garden, retaining the core content of the original curriculum, but with localized innovations based on Chinese schooling policies, traditions and culture, and climate. For example, in Chinese primary schools, class sizes are required to be no more than 45 students per class. Class sizes in various primary schools in the main city of Changsha are around 45–50 students, far larger than class sizes in American primary schools, so changes have to be made to suit the actual situation when designing practical gardening interventions, classroom games and some other interactive sessions. The 24 solar terms are traditional Chinese culture and play an important role in guiding people in their agricultural activities and dietary intake. For example, planting specific types of FV in specific seasons not only has a high survival rate but also yields a large amount of fruit; the intake of specific types of FV in specific seasons can bring various health benefits to the human body, so this component can be added to the curriculum design. Also, in the spring and autumn in Changsha there is a lot of rain and measures should be considered to ensure that the practical horticultural interventions run smoothly during these seasons.

#### 2.6.2. SP Intervention 

The SP intervention is based on the Walk Across Texas program and has been adapted to Chinese school policy while maintaining the core content of the curriculum. In Changsha, schools are required to implement the ‘one hour of school exercise per day’ policy and to instruct students in the skills of emerging sports, so rope skipping as an entrance exam item has become the main form of SP intervention since it is (1) not restricted by space and equipment and is easy to do in schools; (2) both fun and challenging and is conducive; and (3) the intensity of the exercise meets the requirements of MVPA, which has more potential benefits for children physical and mental health. Therefore, rope skipping has been identified as the main form of intervention, and on top of this, some sports competitions and fun games will be incorporated, with prizes and certificates to be awarded to students who achieved their goals or rankings, thus attracting more students to participate in the long term. A sports health course will also be developed, focusing on an overview of sports and emergency management of sports injuries, so that students could enrich their knowledge base while bringing knowledge transfer and first aid help to themselves and to them.

#### 2.6.3. Regular Practice Group

School children in the regular practice group will continue to follow their regular teaching schedule during the study without exposure to any of the intervention components of this study. Immediately after completing one academic year of intervention and follow-up for the intervention group, the control group will receive the same materials related to the intervention components as the intervention group.

### 2.7. Process Evaluation

Process evaluation is important in explaining the reasons for the discrepancies between expected and observed outcomes and in designing and implementing more rational and rigorous intervention program for the future [39]. Throughout the intervention, we will identify the process evaluation elements and procedure based on the principles and steps described in the conceptual framework by Saunders et al. [40], including: (1) frequency and intensity of interventions actually delivered by teachers, volunteers, program team members (dose delivered); (2) student and primary caregivers class attendance will be recorded at the schools to establish exposure and participation in the intervention, logbooks will be recorded to understand how satisfied they are with the intervention (dose received); (3) classroom observations and surveys of teachers, volunteers and program team members to assess the extent to which the intervention is being implemented as intended (fidelity); (4) interviews with school principals, teachers, and volunteers to understand the level of support from schools for the program (context).

### 2.8. Outcome Evaluation

The outcome indicator measure will be administered at three points in time. Firstly, a baseline measurement will be taken prior to randomization to a group of six public primary schools. Then the same measurement will be taken after the completion of the six-month intervention, and a final identical measurement will be taken six months after the completion of the formal intervention period to assess the sustainability of the intervention (6 months after completion of the formal intervention period, as recommended by the National Obesity Observatory). Data collection will be completed by trained data collection workers using paper questionnaires, exercise bracelets, height boards, scales and tape measures for students, and electronic questionnaires and interview guides for parents using those already entered into Questionnaire Star. The specific measurement information is shown in Table 2.

### 2.9. Outcomes Measure

#### 2.9.1. Primary Outcome 

Daily intake of FV (unit: g).Daily minutes of MVPA (unit: minutes).

#### 2.9.2. Secondary Outcome

The children’ FV preferences, identification and the attitude and willingness to eat FV.PA frequency and attitudes of children.Daily sedentary time, video screen time and sleep time (unit: minutes).Parental attitudes towards children’s FV intake and SP.Children’s height, weight and waistline.Questions and recommendations on the implementation of the interventions.

### 2.10. Statistical Analyses

Statistical analysis will be performed using SPSS 26.0 statistical software. According to the data characteristics, the children’s intake of FV, MVPA, and sedentary behaviors and weight status will be statistically described, and the chi-square test and the nonparametric rank-sum test will be used for univariate analysis to compare the differences in intake of FV, MVPA and sedentary behaviors and weight status in the intervention group and the control group. The generalized estimating equation (GEE) will be used to take intake of FV, MVPA and sedentary behaviors and weight status as dependent variables, and at the same time, the interaction between intervention effect and time will be considered to analyze the influence of the gardening intervention on intake of FV, MVPA and sedentary behaviors and weight status. The test level of all analytical methods is α = 0.05 (two-sided), and the difference is considered statistically significant with *p* ≤ 0.05. 

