### 2.3. Sample Size Estimation

With PA duration rate (PA duration > 60 min per day) and FV intake rate (FV intake >700 g per day) as a calculated basis: control group weekly PA and FV intake rate divided into p1 = 20.6% and p1 = 23.1%, it is expected that after the intervention the daily PA hours and FV intake of the intervention group is 50% of the standard, other control groups are not considered for the time being, an alpha of 0.05, power of 90% and 20% of lost visits are considered, the final settlement results: 79 people in each group, a total of 237 people.

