**Dietary behavior**					
Daily intake of FV and food intake frequency	√	√		The Food Frequency Questionnaires, FFQ required for the study was developed using the food frequency questionnaire compiled by the 2016 Chinese Resident Dietary Survey with appropriate adjustments according to the study content and purposes of the study, with Cronbach’s > 0.7.	The questionnaires should be self-reported by parents or other primary caregivers of the students.
Children’s FV preferences, identification and the attitude and willingness to eat FV	√	√		Using the Dutch Eating Behavior Questionnaire child-version, DEBQ-C.Zhao Yan et al.developed the Chinese version of the children’s dietary behavior scale according to the English version of DEBQ-C, with Cronbach’s > 0.7	Students should finish the questionnaires in the classroom in the presence of the trained outcome assessors, who can provide guidance and help.
Parental attitudes towards children’s FV intake and SP	√	√		The questionnaire will be adapted from the nutrition knowledge, attitude and praxis questionnaire (KAP) to evaluate children’s knowledge, attitudes and praxis about FV, with Cronbach’s> 0.7.	Students should finish the questionnaires in the classroom in the presence of the trained outcome assessors, who can provide guidance and help.
**Questions and recommendations on the implementation of the interventions**		√		Interview questions included school climate and barriers to implementation of interventions, perceived benefits and challenges to intervention, opinions and perceptions about the intervention’s effects on student involvement, behaviorand class-related outcomes, beliefs about parental involvement, potential for sustainability, overall recommendations to other school principals and ideas for improvements.	The questionnaires should be filled by the trained investigators after face-to-face interviews with school principals, teachers and volunteers.

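### Section 2.10 names no baseline adjustment for FV intake or MVPA, although both are measured before randomisation; a common-baseline model would be more precise, by an amount the documents do not fix

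*Protocol article*

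**What the plan says.** - **Baseline data.** Section 2.8 states: "Firstly, a baseline measurement will be taken prior to randomization to a group of six public primary schools". Section 2.9.1 defines both primary outcomes as continuous, in grams and in minutes per day. Table 2 ticks baseline for both.
- **Follow-up times.** Table 2 ticks MVPA at baseline, 6 and 12 months. The row "Daily intake of FV and food intake frequency" is ticked at baseline and 6 months only. Section 2.8, however, promises the same measurements again six months after the intervention ends, and section 2.1 has effects assessed at 6 and 12 months.
- **Univariate tests.** Section 2.10: "the chi-square test and the nonparametric rank-sum test will be used for univariate analysis to compare the differences in intake of FV, MVPA". No baseline term is named.
- **Model.** Section 2.10 makes FV intake and MVPA dependent variables in a GEE, and "the interaction between intervention effect and time will be considered to analyze the influence of the gardening intervention on intake of FV, MVPA". It does not say whether baseline is a level of time, a covariate, or constrained to be equal across arms.
- **Sizing.** Section 2.3 takes "control group weekly PA and FV intake rate divided into p1 = 20.6% and p1 = 23.1"% in controls against 50%, and says "an alpha of 0.05, power of 90% and 20% of lost visits are considered". The result is 79 per group, 237 in total. Section 2.2.2 instead recruits 96 children in each of six schools.

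**The concern.** The pre-randomisation value of each primary outcome is usually the best single predictor of its follow-up value. Section 2.10 does not say that it will be used in the efficient way.

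The univariate tests do not use it at all. If baseline enters the GEE as an ordinary time point with arm means left free, the arm-by-time interaction subtracts the whole baseline value from the follow-up value, that is, it applies a slope of 1. When rho is low this adds noise, and below rho = 0.5 it is less precise at child level than ignoring baseline.

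With two schools per arm, chance baseline differences between arms are likely, so how they are handled matters. What is at stake is precision obtainable from data already being collected. The validity of the trial is not in question here.

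**Working it through.** **1. The plan's own sample size.** Two proportions, 23.1% v 50%, two-sided alpha 0.05, power 90%, no continuity correction: 65.2, so 66 per group. 66 × 1.2 = 79.2, which matches the stated 79. The calculation uses dichotomised rates and no baseline correlation, so it neither relies on baseline data nor credits it.

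**2. Evaluable numbers.** The documents support two.
- Section 2.3: 79 × 0.8 = 63 per arm, or 31.5 per school.
- Section 2.2.2: 96 × 2 schools = 192 per arm; 192 × 0.8 = 154, or 77 per school.

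**3. What the interaction estimates.** With two times, complete data and free arm means at baseline, the arm-by-time interaction equals the difference between arms in mean raw change.

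**4. Child-level variance.** Per child, in units of the outcome variance, with equal SDs at both times:
- follow-up only: 1
- raw change: 2(1 − rho)
- baseline-adjusted: 1 − rho²

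Adjusted over raw change = (1 − rho²) / [2(1 − rho)] = (1 + rho)/2, which is below 1 for any rho below 1.

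**5. Power, ignoring clustering.** Rho is assumed. The reference effect is the one detectable with 90% power at 63 per arm: d = (1.960 + 1.282) × √(2/63) = 0.578 SD. Power = Φ(d/√(2v/n) − 1.96), with v from step 4.

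| n per arm | rho | follow-up only | raw change | adjusted | gain over raw change |
|---|---|---|---|---|---|
| 63 | 0.3 | 90.0% | 78.2% | 92.5% | 14 points |
| 63 | 0.5 | 90.0% | 90.0% | 96.3% | 6 points |
| 63 | 0.7 | 90.0% | 98.7% | 99.5% | 1 point |
| 154 | 0.3 | 99.9% | 99.0% | 99.96% | 1 point |
| 154 | 0.5 | 99.9% | 99.9% | over 99.9% | under 1 point |

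**6. Power with school-level inference.** Two schools per arm and three arms leave 6 − 3 = 3 df. For m children per school, school-level correlation rs and child-level rho:
- variance of a school mean: V = ICC + (1 − ICC)/m
- covariance of baseline and follow-up school means: C = ICC × rs + (1 − ICC) × rho/m
- follow-up only V; raw change 2(V − C); optimally weighted baseline V − C²/V
- power from a noncentral t on 3 df, with noncentrality d/√(variance)

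Example with m = 31.5, ICC 0.02, rs 0.8, rho 0.5: V = 0.0511 and C = 0.0316. Raw change is 0.0391 and adjusted is 0.0316. Power is 42% (follow-up only), 51% (raw change) and 59% (adjusted).

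Over ICC 0.01 to 0.05, rs 0.5 to 0.8, rho 0.5, and m = 31.5 or 77, adjustment gains about 5 to 11 points over raw change and about 7 to 28 over follow-up only. The best baseline weight is treated as known throughout.

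**7. When simple adjustment fails.** Using only the child's own baseline slope (0.5) gives variance 1.25V − C. With m = 77, ICC 0.05 and rs 0.95: V = 0.0623 and C = 0.0537. The child-slope variance is 0.0243 against 0.0173 for raw change, and power is 69.7% against 82.1%.

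**The case against.** **The article may simply be silent.** Section 2.10 is one paragraph of a journal article, and a fuller plan may specify covariates and the coding of time. This stands in part. A reader might infer that the plan states baseline to be an outcome time, but it does not. For FV that reading is forced only if Table 2's two ticks are right, and section 2.8 contradicts them. With a 12-month FV value, the interaction could be estimated from follow-up alone. For MVPA, with three ticked times, nothing forces it. Still, section 2.10 does fix a concrete method, and neither a baseline covariate nor a common baseline mean is part of it.

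**Raw change is a legitimate estimator.** This stands. It is unbiased under randomisation, and above rho = 0.5 it already beats a follow-up-only comparison at child level. A reader might infer that the planned analysis is invalid; the documents do not support that.

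**The univariate tests are not declared primary.** This stands. The section labels them univariate and follows them with the model, so their lack of a baseline term matters little if they are descriptive.

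**The size is assumed.** This stands. Rho and the ICC appear nowhere, and the 90% power in section 2.3 concerns dichotomised rates. The reliability of 0.76 that Table 2 gives for MVPA is not a baseline-to-six-month correlation. Quoting only the 14- or 6-point gain would ignore the larger sample in section 2.2.2.

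**Conclusion.** The point holds as one of efficiency. Section 2.10 names no baseline adjustment although both primary outcomes are measured before randomisation. On the natural reading its GEE contrast is raw change, which is valid but less precise than a baseline-adjusted estimate for any rho below 1.

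The direction does not depend on the assumed rho, provided that baseline is weighted well at both child and school level. The size does depend on it:
- about 14, 6 and 1 power points at rho 0.3, 0.5 and 0.7 with 63 per arm and no clustering;
- 1 point or less with about 154 per arm and no clustering;
- about 5 to 11 points with school-level inference under the assumptions in step 6.

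A reader might infer that adjustment would repair the trial's power. It would not. In the worked school-level example even the adjusted analysis reaches only 59%, so having two schools per arm remains the larger limit. Nor is every form of adjustment an improvement, as step 7 shows. The change is worth making but is not critical.

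**What to change.** In section 2.10:
- Take the primary estimate for FV and for MVPA from a longitudinal model that keeps baseline in the outcome vector, with a common baseline mean across arms.
- Let that model allow for school and school-by-time correlation, and base inference on the school level.
- Report the raw-change contrast as a sensitivity analysis.
- State that the chi-square and rank-sum tests are descriptive.
- Do not make adjustment by the child's own baseline slope the sole analysis, because it can lose to raw change when school differences are large and persistent.

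The FV time points in Table 2 and section 2.8 need to be reconciled so that the model's time levels are defined.

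Cost: no new data, visits or children. The modelling is somewhat more work than the GEE now named. With six schools, the school-level part of the baseline weight will be poorly estimated, so the gain actually achieved may fall short of the 5 to 11 points; the sensitivity analysis guards against relying on it.

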### 2.11. Cost-Effectiveness Analysis

We will assess the cost-effectiveness of the program in terms of cost per case of fruit and vegetable intake or MVPA improved. 

Cost: The cost will include the time spent by project staff, school staff and the student’s primary caregiver (in most cases the parent) for all intervention activities and material costs. Only the time spent by project staff implementing the intervention will be included. Time costs will be based on individual employment compensation (if available) or the average compensation for similar employees in the local area. The cost of garden materials, seeds, fertilizer, kitchen utensils, kettles, and hoes are subject to actual purchase prices.

Effectiveness: The impact of the program will be measured by changes in fruit and vegetable intake or MVPA. The cost-effectiveness ratio will be calculated as follows:Cost of intervention services for one primary school child.Cost for each case of improved fruit and vegetable intake.Cost for each case of improved MVPA.

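### The cost-effectiveness ratios count improved children with no comparator term and no definition of an improved case, although the trial has a randomised regular practice arm

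*Protocol article*

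**What the plan says.** Section 2.11 opens with the measure: "We will assess the cost-effectiveness of the program in terms of cost per case of fruit and vegetable intake or MVPA improved". It then says how effectiveness enters: "The impact of the program will be measured by changes in fruit and vegetable intake or MVPA". It announces how the ratio will be computed and lists three quantities: the cost of serving one child, "Cost for each case of improved fruit and vegetable intake", and "Cost for each case of improved MVPA".

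On the cost side, the section counts the time of project staff, school staff and caregivers "for all intervention activities and material costs". The next sentence reads: "Only the time spent by project staff implementing the intervention will be included".

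Two other places matter:

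- Section 2.6.3 describes a concurrent randomised comparator whose children "will continue to follow their regular teaching schedule during the study without exposure to any of the intervention components of this study".
- Section 2.10 compares intervention with control and plans a GEE in which "the interaction between intervention effect and time will be considered".

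Section 2.11 refers to neither. It also speaks of one programme, although section 2.1 sets up two different intervention arms.

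**The concern.** A cost-effectiveness ratio should say what it costs to obtain one more improved child than would otherwise have been obtained. The ratios in section 2.11 contain no difference in cost and no difference in effect. A case of improvement is most naturally a property of one child, judged by that child's own change; a between-arm effect cannot be assigned to a single child. So the plain reading is cost divided by the number of programme children who improved.

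Children will improve without the programme, and the article itself points to reasons:

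- Table 2 marks FV intake at baseline and 6 months, so the two readings fall in different seasons, and section 2.6.1 stresses that planting and eating FV depend on season.
- FV intake is reported by caregivers, and the Discussion concedes that self-report is open to bias.
- Table 2 gives a reliability of 0.76 for MVPA minutes from the wristband, so noise alone will move some children upward.

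The regular practice arm would absorb these influences, but the ratios do not use it. At stake is a cost figure that makes each additional child helped look cheaper than it is, and that would return an ordinary-looking number even if the programme did nothing.

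**Working it through.** **The plan's own figures.** The article gives no cost-effectiveness figure to reproduce. The only relevant rates are the planning rates in section 2.3: 23.1% (FV above 700 g/day) and 20.6% (activity above 60 min/day) in control, and 50% under intervention. To confirm how they are used, take FV with unpooled variance, two-sided alpha 0.05 and power 0.90:

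n = (1.960 + 1.282)² × [0.231 × 0.769 + 0.50 × 0.50] / (0.50 − 0.231)² ≈ 62.1, rounded up to 63.

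63 / (1 − 0.20) = 78.75, rounded up to 79 per group, and 3 × 79 = 237. This matches section 2.3, so 23.1% and 50% are the shares compared.

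**Formulas.** Let C be the programme cost per child, pI the share improved in an intervention arm and pC the share improved under regular practice. Assume regular practice has no extra cost.

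- Ratio without comparator: C / pI
- Incremental ratio: C / (pI − pC)
- Understatement factor: pI / (pI − pC)

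The factor exceeds 1 whenever 0 < pC < pI. If pI = pC, the incremental ratio is undefined, while C / pI is still finite.

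**Illustration.** The section 2.3 rates are shares above a threshold. They are used here only as a stand-in for shares improved.

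| Outcome | pI | pC | C / pI | C / (pI − pC) | Factor |
|---|---|---|---|---|---|
| FV | 0.50 | 0.231 | 2.00C | C / 0.269 = 3.72C | 1.86 |
| Activity | 0.50 | 0.206 | 2.00C | C / 0.294 = 3.40C | 1.70 |

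With 79 children in an arm, 79 × 0.50 = 39.5 cases would be credited, against 79 × 0.269 = 21.3 (FV) or 79 × 0.294 = 23.2 (activity) in excess of control.

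**Range.** Keeping pI = 0.50 and assuming other control shares:

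| pC (assumed) | Factor |
|---|---|
| 0.10 | 1.25 |
| 0.20 | 1.67 |
| 0.30 | 2.50 |
| 0.40 | 5.00 |

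**Counter-check.** Suppose effectiveness meant the net rise in the share above the threshold, intervention children started at the control rate, and controls did not change. For FV the denominator would be 0.50 − 0.231 = 0.269, the same as the incremental one, and the factor would be 1.0. So the size depends on what a case is and on how much controls change. The article gives neither.

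**The case against.** The best reply is that section 2.11 is loose rather than wrong. It does not say that cost is divided by every child who improves, nor that change is before-after. Impact is a causal word and could mean change relative to control. Section 2.10 already specifies a between-arm analysis of both outcomes, and a condensed article may leave economic detail to a fuller document. The analysis is not among the outcomes in section 2.9.

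Much of this stands. A reader might infer that the plan commits to an uncontrolled before-after ratio over all improvers. The text does not support that, because neither the case nor the arms in which cases are counted are defined. A reader might also take 1.9 as the bias in this trial. It is not, since threshold shares are not shares improved, and the counter-check gives 1.0 under another reading. Finally, a reader might infer from the staff-time sentence that school staff and caregiver time are dropped. The sentence can equally mean that, within project staff time, only implementation time counts, so this is a matter of wording.

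What does not stand is that the article is merely silent. It announces a calculation and lists its terms. Those terms contain no comparator and no link to section 2.10, so an analyst who follows them as written credits to the programme improvement that would have occurred anyway.

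**Conclusion.** The concern holds in this form: section 2.11 sets cost per improved case without a comparator and without defining a case, in a trial that has a randomised comparator. On the plain reading the direction of error is certain whenever some control children improve and the programme has a positive effect: cost per additional child helped is understated. With no effect the ratio remains finite and does not reveal the failure.

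The size is not known. Factors of about 1.9 (FV) and 1.7 (activity) illustrate it, on two assumptions: that the planning rates stand in for shares improved, and that regular practice costs nothing extra. The point concerns a supporting economic analysis; the primary comparison of FV intake and MVPA is untouched. It should be corrected because the remedy is cheap and the correct comparison is already available.

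**What to change.** In section 2.11:

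1. Replace the two cost-per-case ratios with incremental ones: (mean cost in arm − mean cost in comparator) / (effect in arm − effect in comparator), with the effect taken from the randomised between-arm comparison.
2. Give this ratio for each intervention arm against regular practice. Add combined against sports participation alone if the added value of gardening and cooking is to be claimed.
3. Define an improved case for FV intake and for MVPA, stating the criterion and the time point.
4. Reword the staff-time sentence so that it does not appear to remove the school staff and caregiver time that the preceding sentence includes.

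The cost is a few sentences and slightly more analysis, with no new outcome data. The ratio will probably look less favourable, and it will have no meaningful value if there is no effect.
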